### Control group

Parent(s)/caregiver(s) in the control group of the study receive ‘care-as-usual’ as provided by the Youth Health Care Centers. Parents are invited to visit the Youth Health Care centers for regular well-child check-ups offered by preventive Youth Health Care at set ages (12 check-ups in the first 18 months after childbirth). During these check-ups of twenty minutes, the child’s growth and development are monitored and common advice regarding parenting, development, and growth of children is given (e.g. oral information and generic information leaflets). If needed, parents can be referred to specialized professional care (e.g. social work or medical care).

### Data collection

Data from parent(s)/caregiver(s) in both research groups will be collected at child age 1–3 months (i.e. baseline), at age 12 months (a brief questionnaire) and 18 months (i.e. follow-up). Parents receive self-report questionnaires assessing demographic characteristics, child characteristics (e.g. gender, preterm, low birthweight) and outcomes. Furthermore, nurse characteristics (e.g. personal and work-related) and the working alliance between parent and nurse are assessed by a self-report questionnaire as well. All questionnaires consist of evidence-based instruments, which are described in the measurements section.

Data are handled according to the guidelines of the Dutch Data Protection Authority [20].

### Measurements

#### Primary outcome measurements

The primary outcomes of this study are various elements of empowerment: social support, parenting skills, self-sufficiency, resilience and behavioral and emotional problems of the child at 18 months.

Social support and parenting skills are measured by the Parenting Stress Questionnaire (in Dutch: Opvoedingsbelasting vragenlijst) [21] and the Family Functioning Questionnaire (in Dutch: Vragenlijst Gezinsfunctioneren Ouders) [22]. The Parenting Stress Questionnaire consists of 34 items. Each item is accompanied by a 4-point response scale with 1 = *not true*, 2 = *somewhat true*, 3 = *quite true*, and 4 = *very true.* Five subscales are computed: problems in parent-child relation (six items), problems with parenting (seven items), depressive moods (seven items), role limitations (six items) and health problems of the parent (eight items). Considering the age of the children in this study at baseline, all items of the subscale “problems with parenting” were not included in the baseline questionnaire because the items assess parenting factors that are not applicable to newborn children. Subscale scores are calculated by summing the individual items belonging to a subscale and thereafter converting the subscale scores into T-scores, using the Dutch reference values. For all subscales, scores between T = 30–65 indicate that there are no problems, scores between T = 66–69 indicate moderate problems, and scores of T= > 69 indicate serious problems.

The Family Functioning Questionnaire consists of 28 items. Each item is accompanied by a 4-point response scale with 1 = *not true*, 2 = *somewhat true*, 3 = *quite true*, and 4 = *very true*. Five subscale scores are computed: basic care of the child (seven items), parenting (seven items), social contacts (five items), experience of parent’s own childhood (four items) and partner relation (five items). Considering the age of the children in this study at baseline, no items of the subscale “parenting” were included in the baseline questionnaire because the items assess parenting factors that are not applicable to newborn children. Subscale scores are calculated by the summing the individual items belonging to a subscale and thereafter converting the subscale scores into T-scores, using the Dutch reference values. For all subscales, a score between T = 0–31 indicates problems.

Self-sufficiency is measured by the Empowerment Questionnaire (EMPO) *parents, version* 2.0 (in Dutch: Vragenlijst Empowerment (EMPO) *ouders, versie* 2.0) [23]. The questionnaire consists of 27 items. Each item is scored on a 5-point scale with 1 = *strongly disagree*, 2 = *disagree*, 3 = *neither agree, nor disagree*, 4 = *agree*, and 5 = *strongly agree*. Items can be allocated to three subscales: perceived competence as a person (eight items), perceived competence as a parent (seven items) and utilization of competence (12 items). Considering the age of the children in this study at baseline, five items (three items of the subscale “perceived competence as a parent” and two items of the subscale “competence utilization”) were not included in the baseline questionnaire because the items assessed factors that are not applicable to newborn children. Subscale scores are calculated by the sumscores of the individual items belonging to that subscale and thereafter converted into scores between 1 and 10. A low score indicates problems.

Resilience is measured by the Resilience Scale – Dutch version [24]. The questionnaire consists of 25 items. Each item is scored on a 4-point scale with 1 = *strongly disagree*, 2 = *disagree*, 3 = *agree*, and 4 = *strongly agree*. Items can be allocated into two subscales: personal competence (17 items) and acceptance of self and life (eight items). The minimum total score is 25, the maximum total score is 100 with higher scores indicating higher resilience.

Behavioral and emotional problems of the child at 18 months is assessed by the Child Behavior Checklist (CBCL) for ages 1½–5 [25]. The CBCL consists of 99 items. Each items is scored on a 3-point scale with 0 = *not true*, 1 = *somewhat or sometimes true*, and 2 = *very true or often true*. The scoring gives a summary profile (internalizing, externalizing, and total problem scores), a syndrome profile (emotionally reactive, anxious/depressed, somatic complaints, withdrawn, sleep problems, attention problems, and aggressive behavior) and five scales (affective problems, anxiety problems, pervasive developmental problems, attention deficit/hyperactive problems, and oppositional defiant problems) oriented at the Diagnostic and Statistical Manual for Mental Disorders (DSM). A T-score of ≥63 for summary scales and ≥70 for syndrome and DSM-oriented scales, are considered clinically significant. Scores between 60 and 63 for summary scales or between 65 and 70 for syndrome and DSM-oriented scales are considered as borderline clinically significant. Scores under 60 or 65 are considered non-clinical [25].

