### Objective

A controlled trial is performed to investigate the effectiveness of the Supportive Parenting intervention in empowering parent(s)/caregiver(s) who are at risk of parenting problems in terms of social support, parenting skills, resilience, and self-sufficiency. Furthermore, we will explore which parent, child, and nurse characteristics are related to the effects of the intervention Supportive Parenting on the empowerment of parent(s)/caregiver(s) at risk of parenting problems. Additionally, interviews and focus group interviews are performed to investigate the factors that promote/hinder a broader implementation (e.g. among parents with older children [>18 months], during pregnancy, among different ethnic groups) of the intervention Supportive Parenting.

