### Power of the study

Two Youth Health Care centers participate in the study. Their teams invited 313 parents (for the intervention group) and 2346 parents (for the control group). Taking into account informed consent by 50 % and eligibility of 10 % to participate in the study for the control group, we expect data of 157 parents in the intervention group and 117 parents in the control group.

With the use of continuous measures and assuming a standard deviation of 1.00 in both groups, a power of 0.80 and an alpha of 0.05, these group sizes are sufficient to demonstrate a significant difference of 0.35 between the intervention group and the control group. This is appropriate to indicate relevant effects [31, 32].

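### Five primary domains are spread over 31 possible scores, with no primary score named for any domain and no statement of which outcomes are dichotomised

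*Protocol article*

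**What the plan says.** In the Protocol article, Primary outcome measurements opens with "The primary outcomes of this study are various elements of empowerment: social support, parenting skills, self-sufficiency, resilience and behavioral and emotional problems" of the child, assessed at 18 months. It gives no lead domain, composite or order.

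The same section then describes the instruments:

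- **Social support and parenting skills** share two questionnaires. For the Parenting Stress Questionnaire: "Five subscales are computed: problems in parent-child relation (six items), problems with parenting (seven items), depressive moods (seven items"), followed by role limitations and the parent's health problems. For the Family Functioning Questionnaire: "Five subscale scores are computed: basic care of the child (seven items), parenting (seven items), social contacts (five items"), followed by the parent's own childhood and the partner relation. No subscale is assigned to either domain.
- **Self-sufficiency** uses the EMPO: "Items can be allocated to three subscales: perceived competence as a person (eight items), perceived competence as a parent (seven items"), plus utilization of competence.
- **Resilience** has two subscales and a total.
- **Child problems** use the CBCL: "The scoring gives a summary profile (internalizing, externalizing, and total problem scores), a syndrome profile" of seven scales and five DSM-oriented scales.

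Statistical analysis assigns linear regression to continuous outcomes and logistic regression to dichotomised ones, without saying which outcomes are which. Power of the study refers to unnamed continuous measures, "assuming a standard deviation of 1.00 in both groups, a power of 0.80 and an alpha of 0.05", and gives a detectable difference of 0.35 with 157 and 117 parents.

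The Objective describes empowerment "in terms of social support, parenting skills, resilience, and self-sufficiency", without the child outcome. Study hypothesis states the same four elements and adds the child outcome as a further hypothesis.

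**The concern.** A primary outcome should tell the reader in advance which result would confirm or refute the hypothesis. Here it does not. For social support and parenting skills in particular, a reader cannot tell which of ten subscales counts. Some, such as the parent's health problems or the experience of the parent's own childhood, do not on their face measure either construct.

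Followed as written, the article would let effectiveness be claimed from whichever score, or whichever continuous or dichotomised form, turned out favourably. The only alpha it states is 0.05, in the power paragraph, and that paragraph is tied to no named score. Whether the child outcome is an element of empowerment, a separate primary outcome or an additional one also depends on the section read.

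**Working it through.** **Count of scores.** Parenting Stress 5 + Family Functioning 5 + EMPO 3 + Resilience 3 (two subscales and total) + CBCL 15 (3 summary, 7 syndrome, 5 DSM-oriented) = 31. Numeric cut-offs are given for 5 + 5 + 15 = 25 of these. None is given for EMPO or the Resilience Scale.

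**The plan's own figure.** Group sizes: 313 × 0.5 = 156.5 and 2346 × 0.5 × 0.1 = 117.3, matching 157 and 117. With SD 1, SE = √(1/157 + 1/117) = 0.1221. Detectable difference at two-sided 5% and 80% power: (1.960 + 0.842) × 0.1221 = 0.342. Power at 0.35: Φ(0.35/0.1221 − 1.960) = 0.82. The stated 0.35 reproduces. A one-sided test would give 0.304, so two-sided is assumed below.

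**Five scores.** The first Holm step uses alpha 0.05/5 = 0.01. Detectable difference: (2.576 + 0.842) × 0.1221 = 0.417. Power at 0.35: Φ(0.35/0.1221 − 2.576) = 0.61.

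**Chance of at least one p < 0.05 with no effect on any score, unadjusted.** For k independent tests this is 1 − 0.95^k. For equally correlated normal test statistics with correlation ρ and c = 1.96, it is 1 − ∫ φ(g) [Φ((c − √ρ g)/√(1 − ρ)) − Φ((−c − √ρ g)/√(1 − ρ))]^k dg. The documents give no correlations, so every ρ is an assumption.

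| ρ | 5 scores | 31 scores |
|---|---|---|
| 0 | 23% | 80% |
| 0.3 | 21% | 67% |
| 0.5 | 18% | 51% |
| 0.7 | 15% | 34% |
| 0.9 | 10% | 17% |

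A simulated block structure (correlation 0.5–0.8 within an instrument, 0.2–0.5 between instruments) gives 43–65% for 31 scores. The expected number of false positives over 31 tests is 31 × 0.05 = 1.55 at any correlation.

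**Dichotomised outcomes.** Assume a normal score shifted by 0.35 SD and cut where a share p of controls has the problem. The intervention share is then Φ(z(p) − 0.35). The prevalence p is an assumption.

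| Control share | Intervention share | Power, 117 v 157 |
|---|---|---|
| 10% | 5.1% | 34% |
| 20% | 11.7% | 48% |
| 50% | 36.3% | 62% |

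The continuous score has 82% power for the same shift.

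**The case against.** The strongest reply is that an article condenses a fuller protocol, and that a multiplicity rule belongs in an analysis plan that is not shown. That stands: the absence of such a rule is not held against the plan here. It does not answer the main point. Naming the primary outcome is the protocol's own task, and this article spends a full section on it without naming a score.

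Four stronger readings are tempting, and the documents do not support them:

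- A reader might infer that all 31 scores will be tested at 5%. The article does not say so. Alpha 0.05 appears only in the power paragraph, and much of the outcome text describes what the questionnaires yield rather than a list of tests.
- A reader might conclude that a false positive is near certain, taking the 80%. That needs independence, which overlapping scores rule out: the Resilience total is made of the items of its two subscales (17 + 8 = 25), and the CBCL totals overlap their components. At high correlation the figure falls to 34% or 17%.
- A reader might say that the power figure fits none of the outcomes. In SD units it fits any single continuous score.
- A reader might suppose that every score can be dichotomised, or that the child outcome was an afterthought. Cut-offs exist for 25 of the 31. Study hypothesis and Study design both include the child outcome, so only its status is inconsistent.

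**Conclusion.** The concern holds as a defect in how the primary outcome is defined: five domains, 31 possible scores, no primary score for any domain, ten subscales not mapped to two of the domains, an open choice of form, and a child outcome whose status varies between sections.

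The size is conditional. It rests on no true effect, unadjusted testing at two-sided 5%, and assumed correlations. Under moderate correlations the chance of at least one false positive is about 40–65% if all 31 are tested. If only one score per domain is tested it is about 18–23%, which is still well above 5%. The 0.35 SD figure is right for one continuous score tested alone. It does not extend to a family of five (61% power at 0.35 at the first Holm step) or to a dichotomised outcome (about 34–62%, for assumed prevalences of 10–50%). None of these figures allows for loss by 18 months.

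**What to change.** Name one continuous score per domain as primary. An example set:

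- **Social support:** Family Functioning social contacts.
- **Parenting skills:** one subscale that was also measured at baseline. Parenting Stress problems with parenting and Family Functioning parenting are unsuitable, because their items were left out at baseline and the baseline correction in Statistical analysis would be impossible. The parent-child relation and basic care subscales are not reported as omitted.
- **Self-sufficiency:** one specified EMPO subscale. The five EMPO items omitted at baseline come from the other two subscales, so only perceived competence as a person is complete at both times.
- **Resilience:** Resilience Scale total.
- **Child problems:** CBCL total problems.

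Test the five with Holm at an overall 5%, or cite the rule in the analysis plan if one already exists. Make all other subscales and every dichotomised version secondary, and list which outcomes are dichotomised. Align the child outcome's status across Objective, Study hypothesis and Primary outcome measurements. In Power of the study, keep 0.35 SD for a single score and add that at the first Holm step the detectable difference is about 0.42 SD, with 61% power at 0.35, before any loss to follow-up.

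This changes wording only, with no new data or visits. The downside is a less favourable stated detectable difference (0.417 against 0.342).

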#### Other measures

Parent characteristics that are assessed include various demographic factors (age, country of birth, income in euros, educational level, employment situation, and family structure). Additionally, the intervention group completes questions on the amount of home visits they have received, and their satisfaction with the intervention, to check for adherence to intervention protocols. Each questionnaire contains an open space for parents to write down comments and questions with regard to the study and the intervention.

Professional characteristics that are assessed are personality, measured by the Brief HEXACO Inventory [26] and work-related factors, measured by the Utrechtse Burnout Scale [27]. Both the Youth Health Care nurse and parents complete the Working Alliance Inventory (in Dutch: Werkalliantie Vragenlijst [WAV]) to assess the quality of the relation between parent and nurse [28].

Child characteristics which are assessed are gender, preterm, low birthweight and temperament. Temperament of the child is measured by an adapted version of six scales of the Infant Behavior Questionnaire – Revised (IBQ-R) [29] as used in a study by Roza et al. [29]. The IBQ-R asks parents to rate the frequency of specific behaviors observed during the past week. The adapted version of the IBQ-R uses six of the 14 scales because these scales are judged by Roza et al. [30] to be the most important for the later prediction of the most prevalent behavioral problems in children (e.g. anxiety, aggressive behavior and attention problems). The six scales in the adapted version include Activity Level, Distress to Limitations, Fear, Duration of Orienting, Recovery from Distress and Sadness. Based on the results of the pilot study carried out by Roza et al. [30], the original 7-point scale was adapted to a 3-point scale with 0 = *never present*, 1 = *sometimes present* and 2 = *often present.* This was done, because respondents rarely used the extreme points of scales. Higher scores on the scales, except on the Falling Reactivity scale, indicate more difficult behavior. The scores for each scale were calculated by dividing the sum of the items by the number of completed items [30].

### Power of the study

Two Youth Health Care centers participate in the study. Their teams invited 313 parents (for the intervention group) and 2346 parents (for the control group). Taking into account informed consent by 50 % and eligibility of 10 % to participate in the study for the control group, we expect data of 157 parents in the intervention group and 117 parents in the control group.

With the use of continuous measures and assuming a standard deviation of 1.00 in both groups, a power of 0.80 and an alpha of 0.05, these group sizes are sufficient to demonstrate a significant difference of 0.35 between the intervention group and the control group. This is appropriate to indicate relevant effects [31, 32].

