### Statistical analysis

Descriptive statistics will be used to describe the characteristics of the sample. Linear regression will be used for the evaluation of continuous outcomes and logistic regression for dichotomized outcomes. Research condition (i.e. intervention or control group), will be entered in the model as the independent variable. Where relevant, models will be corrected for the baseline measurements (data of baseline questionnaire) and for potential confounders (age of child and parent, educational level of parents and ethnic background). Additionally, moderation of intervention effects by sociodemographic characteristics (educational level, income and ethnic background) is explored by adding an interaction term to the regression model.

Missing data on the questionnaires will be handled according to the questionnaire protocol.

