A challenge of this study may be the relative high risk intervention group. Parents at risk of parenting problems are a challenging group to reach and are often hesitant to participate in research [34]. However, through close collaboration with the Youth Health Care centers and the Youth Health Care nurses who provide the intervention Supportive Parenting, it is possible to realize participation of this important group of parents.

In conclusion, this paper describes the design of a controlled trial on the prevention of parenting problems by targeting the empowerment of parent(s)/caregiver(s).

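### The 80% power for a difference of 0.35 is calculated on parents expected to consent at baseline, with no allowance for loss before the 18-month outcomes

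*Protocol article*

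**What the plan says.** The protocol article, section Power of the study, reports 313 parents invited for the intervention group and 2346 for the control group. It then reduces these numbers: "Taking into account informed consent by 50 % and eligibility of 10 % to participate in the study for the control group". The result is "we expect data of 157 parents in the intervention group and 117 parents in the control group". With "assuming a standard deviation of 1.00 in both groups", and "a power of 0.80 and an alpha of 0.05", it concludes that "these group sizes are sufficient to demonstrate a significant difference of 0.35 between the intervention group and the control group".

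The two inclusion-procedure sections show what consent means here. In both groups the parent returns the consent form by post together with the baseline questionnaire. The section on primary outcome measurements and the study hypothesis place the outcomes at child age 18 months. Under Statistical analysis, the plan is regression on research condition, corrected for baseline measurements and confounders where this is relevant.

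**The concern.** A power statement for an 18-month comparison should rest on the parents who will have an 18-month measurement. Here the factors applied are consent and, in the control group, eligibility, and both act at entry. Nothing is taken off for parents who consent, complete the first questionnaire and do not return the last one. The article itself says that the programme is voluntary and can be discontinued, and it regards the target group as hard to reach, so complete follow-up is a strong assumption to leave unstated.

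What is at stake is how a null result is read. If the published design says 80% power for 0.35, a non-significant result will be taken as reasonable evidence against an effect of that size. If follow-up is materially incomplete, an unadjusted comparison gives that reassurance only for a larger effect.

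**Working it through.** **Inputs from the article (Power of the study):** 313 and 2346 invited; 50% consent; 10% eligible in the control group; SD 1.00; power 0.80; alpha 0.05; difference 0.35. Sidedness is not stated, so I take two-sided. **Assumed by me:** the loss rates and the baseline correlations, because the article gives neither.

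**1. Group sizes.** 313 × 0.50 = 156.5, stated as 157. 2346 × 0.50 × 0.10 = 117.3, stated as 117. The products account for the stated sizes in full, so there is no hidden allowance for loss.

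**2. The plan's own figure.** Detectable difference = (1.960 + 0.842) × SD × √(1/n₁ + 1/n₂) = 2.802 × √(1/157 + 1/117) = 2.802 × 0.1221 = 0.342. Power at 0.35 = Φ(0.35/0.1221 − 1.960) = Φ(0.906) = 81.7%. A t-test calculation gives 0.343 and 81.5%. A one-sided test would give 0.304, so the two-sided reading is the one that fits. The stated 0.35 is reproduced for 157 v 117 parents with complete data.

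**3. How much loss the margin absorbs.** With equal proportional loss d in both groups, the detectable difference becomes 0.3422/√(1 − d). Setting this to 0.35 gives d = 1 − (0.3422/0.35)² = 0.044. So 80% power needs about 95% to 96% of consenters to be measured at 18 months.

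**4. Assumed range of loss, no covariate adjustment** (calculated on unrounded counts):

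| Loss | Parents at 18 months | Detectable difference | Power at 0.35 |
|---|---|---|---|
| 0% | 157 v 117 | 0.342 | 81.7% |
| 5% | 149 v 111 | 0.351 | 79.8% |
| 10% | 141 v 105 | 0.361 | 77.6% |
| 20% | 126 v 94 | 0.383 | 72.7% |
| 30% | 110 v 82 | 0.409 | 66.9% |

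**5. What baseline adjustment could recover.** With correlation ρ between the baseline and 18-month scores, the residual SD is √(1 − ρ²). Power at 0.35 then stays at 80% or more up to d = 1 − (0.3422/0.35)² × (1 − ρ²). This is 13% for ρ = 0.3, 20% for ρ = 0.4 and 28% for ρ = 0.5.

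**6. Where that recovery is not available.** The child behaviour checklist is described only at 18 months. The parenting subscale of the Family Functioning Questionnaire and the subscale on problems with parenting of the Parenting Stress Questionnaire were left out at baseline. For these outcomes there is no baseline score of the same measure to adjust for.

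**The case against.** The best defence is that the calculation is correct for its inputs and that the article gives no loss rate, so any shortfall comes from a rate the critic supplies. At 10% loss the power is 78% rather than 80%, which is a small difference. Rounding 0.342 up to 0.35 also leaves some room. In addition, the planned baseline adjustment is not used in the power calculation and could restore what is lost. All of this stands. It makes the shortfall conditional, and smaller for scales with a usable baseline score. It does not remove the mismatch between the parents counted and the parents to be analysed, and it gives no help to the three measures without a baseline score.

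A reader might infer several stronger things that the documents do not support.

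- *That the design does not achieve 0.35.* This is not shown. It depends on retention and on baseline correlation, and the article states neither.
- *That the control group will be smaller than 117 because at-risk parents consent less often.* The Discussion does say that "Parents at risk of parenting problems are a challenging group to reach and are often hesitant to participate in research". But that remark introduces the intervention group as the challenge, and the article goes on to say that close collaboration with the centres makes participation feasible. Control parents are scored for risk only after consent, so the 10% may already be the at-risk share among consenters. Its source is not given.
- *That the analysis will be a biased complete-case comparison needing imputation.* The only rule shown is "Missing data on the questionnaires will be handled according to the questionnaire protocol". In a condensed article, the handling of lost participants is commonly left to the full protocol or analysis plan, and its absence here is no error. Complete-case regression is also not necessarily biased: it depends on what drives the loss.
- *That clustering within teams lowers power further by a known amount.* That is a separate question, and the documents give no intraclass correlation from which to size it.

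**Conclusion.** The point holds in a limited form. The stated power is arithmetically correct for 157 v 117 parents with complete 18-month data, but those numbers are expected consenters at baseline. In an unadjusted two-sided comparison with SD 1.00, the claim survives only about 4.4% loss. If 10% to 30% were lost, equally in both groups, power at 0.35 would be 78% to 67% and the detectable difference 0.36 to 0.41. These loss rates are assumptions, not findings about the trial. For outcomes with a baseline score, a correlation of 0.3 to 0.5 would offset loss of 13% to 28%. For the child behaviour checklist and the two omitted parenting subscales, the unadjusted figures are the relevant ones as far as baseline correction is concerned.

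**What to change.** Restate the power paragraph on the number of parents expected to have an 18-month outcome. The article describes invitation in the past tense, so the numbers actually enrolled should replace the 50% and 10% projections. Multiply them by a stated retention and give the resulting detectable difference at 80% power. On the present projections that would be 0.38 at 80% retention (126 v 94). If the authors wish to count on baseline adjustment, they should state the assumed correlation and limit that figure to outcomes that have a baseline score.

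Recruiting more is not the proposal. Holding 157 v 117 at 18 months under 20% loss would have needed 197 v 147 at baseline (157/0.8 and 117/0.8, rounded up), and invitation is finished. The cost is one rewritten paragraph and a slightly less favourable stated figure. In return, readers will know which size of effect a null result can reasonably speak against.
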